## Methods and analysis

### Study design, setting and participants

This prospective, self-controlled, non-intervention, multicentre cohort study investigates the acute effects of slamming-induced impact exposure on high-speed boat operators’ musculoskeletal systems and cognitive functions. The study protocol is reported according to Strengthening the Reporting of Observational Studies in Epidemiology guidelines and was registered prospectively on ClinicalTrials.gov with the identifier NCT05299736.^22^ This study has been designed by the North Atlantic Treaty Organization (NATO) Science & Technology Organization, Research Task Group HFM-344. The recruitment of academic centres started in 2022 and the first participant was enrolled on 23 August 2024. We expect to close the inclusion of study participants before 30 June 2027. The schedule of participant enrolment, exposures and assessments is presented in table 1.

**Table 1 T1:** Schedule of enrolment, exposures and assessments

Timepoint	Study period							
	Enrolment	Allocation	Post allocation					Close-out
	*−t_1_*	0	*t_1_*	*t_2_*	*t_3_*	*t_4_*	*etc*	*t_90_*
Enrolment:								
Eligibility screen	X							
Informed consent	X							
Allocation		X						
Exposure:								
Slamming forces								
Whole body impacts								
Assessments:								
Questionnaire		X						X
Level of pain (VAS)		X	X	X	X	X	X	X
Pain character (pain drawing)		X	X	X	X	X	X	X

Timepoints *t* define days 1–90.

VAS, Visual Analogue Scale.

Eligible participants are military and civilian agencies, organisations and institutions that operate boats capable of hydroplaning speeds, have professional high-speed boat operators and allow the installation of accelerometer devices and data recording. The study will include operators in each centre between age 18 and 65 years who either operate or are being regularly transported onboard high-speed boats and have signed the informed consent form.

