### Outcomes, data sources and measurements

#### Pain

Pain is a common symptom experienced by high-speed boat operators exposed to repeated slamming impacts, and it is a common reason that operators seek medical attention or modify their work activities.^1^ By studying the occurrence and duration of pain and its correlation in time after slamming-induced impacts, the study aims to assess the risks of injurious exposure. Pain can be monitored non-invasively using validated methods, such as the Visual Analogue Scale (VAS) or Numeric Rating Scale, which rate pain intensity, and pain drawings to assess pain location, duration and interference with activities.

In this study, self-reported pain will be logged daily through a smartphone application, PainDrawing (figure 1),^23^ adapted specifically for this project.^24^ The application is based on the Nordic Minister Council’s pain drawing form and a VAS. PainDrawing can be downloaded freely from Google Play and Apple AppStore and works offline and in flight mode. Reported pain data will comprise the following characteristics: location, pain modality, intensity and duration. Participants will be urged to log pain daily for the whole test period, regardless of whether they have been on board a boat or not. Participants will serve as their own controls by comparing periods of exposure onboard with periods of not working onboard.

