### Target sample size

A recent systematic review of five studies reported 1.1 injuries per person per year serving as high-speed boat operators.^5^ Our study follows operators for at least 2 months, estimating that one of six operators may experience one acute episode with musculoskeletal injury. The Minimally Clinically Important Difference for back pain VAS is 14 mm, and the SD is 20 mm.^27^ Consequently, a minimum number of 192 participants would be necessary to reach 80% power (1 minus type II error probability) at a 0.05 significance level (type I error probability) if followed for 2 months.

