### Statistical methods

We will report descriptive statistics and calculate the mean, SD and range for human impact exposure and pain scores. Peak acceleration values, m/s^2^, will be registered in all three axes, x, y and z. A data analysis engine will categorise impacts with various combinations of the impact characteristics and allow for calculating correlations to registered pain experiences and various variables of the reported pain. We will use Pearson correlation coefficients to examine the association between human impact exposure and pain scores. We will also use linear regression to examine these associations while controlling for potential confounding variables (eg, age, sex, body mass index). Multivariate analysis based on analysis of variance (ANOVA) and logit models will be used to identify which characteristics of the impacts correlate to reported pain of various intensities, locations and durations after exposure. The results of the statistical analysis are expected to indicate which impact characteristics show a correlation to reported experiences of pain. Based on these findings, we will establish which impact exposure levels and characteristics are safe regarding physical and cognitive capabilities.

This analysis can also validate alternative ways of quantifying human exposure to discrete whole-body impacts and their potential relevance for predicting the risk of injury. Candidates for alternative units include calculated kinetic energy transferred or absorbed, J/kg, and the speed of this transfer, mechanical power, J/(kg·s). The analysis may need to include the calculated total change of speed and the distance during which the retardation of the boats and the human bodies occurs in each impact.

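### Pain duration is to be analysed with ANOVA and logit models, which take no account of episodes still open when a participant's logging ends at study day 90

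*Protocol article*

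**What the plan says.** Pain duration is both collected and analysed. The Pain section of the protocol article states: "Reported pain data will comprise the following characteristics: location, pain modality, intensity and duration". It builds the assessment of injurious exposure on it: "By studying the occurrence and duration of pain and its correlation in time after slamming-induced impacts".

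The Statistical methods section then gives the method: "Multivariate analysis based on analysis of variance (ANOVA) and logit models will be used" to find which impact characteristics "correlate to reported pain of various intensities, locations and durations after exposure". That sentence is the only one in the section that names duration. Pearson correlation and linear regression are stated for pain scores.

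Observation ends on a fixed study day for each participant. Table 1 schedules the VAS and the pain drawing from allocation to a close-out at t90, and its note reads "Timepoints *t* define days 1–90". The Pain section ties logging to the same window: "Participants will be urged to log pain daily for the whole test period". Nothing in the article continues the log for a participant who is still in pain at close-out, and nothing treats such an episode as incomplete.

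The Target sample size section adds: "Our study follows operators for at least 2 months".

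**The concern.** The length of an episode is known only if the episode ends before the log does. For an episode still open at the last log, the data show a lower bound. ANOVA on the logged length treats that bound as the full duration. A logit on whether pain exceeded a given number of days counts an open episode as a non-event if the log closed before the threshold was reached.

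Both errors act in one direction, and they are larger for longer pain. The episodes most relevant to calling an exposure harmful lose the most, and groups with truly different durations look more alike. The Statistical methods section intends to use these results to decide which exposures are safe, and the Discussion foresees suggesting exposure limits for training. A bias that hides persistent pain is therefore on the unwelcome side.

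**Working it through.** **The plan's own figure.** The only calculated figure nearby is the sample size. Its inputs, from Target sample size, are a difference of 14 mm, SD 20 mm, alpha 0.05 (two-sided assumed), power 80%, and one operator in six with an episode.

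- Per group: 2 × (20 × (1.960 + 0.842) / 14)² = 32.04.
- Total: 32.04 × 6 = 192.2, which reproduces 192.

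This rests on VAS intensity. Duration does not enter it, so the point below leaves it unchanged.

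**Inputs for the duration check.** The window is T = 90 days (Table 1). The documents give no episode length, so the mean duration m is an assumption, shown over a range. Onset is assumed uniform over the 90 days.

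**Exponential durations.**

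- Share open at day 90 = (m/T) × (1 − exp(−T/m)).
- Mean recorded length = m × (1 − share open). The relative understatement of the mean therefore equals the share open.

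Example with m = 30: (30/90) × (1 − exp(−3)) = 0.333 × 0.950 = 0.317, and 30 × (1 − 0.317) = 20.5 days.

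| Assumed mean (days) | Share open at day 90 | Mean recorded (days) |
|---|---|---|
| 3 | 3% | 2.9 |
| 7 | 8% | 6.5 |
| 14 | 16% | 11.8 |
| 28 | 30% | 19.6 |
| 30 | 32% | 20.5 |
| 42 | 41% | 24.7 |

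**Sensitivity to the exponential shape.** If every episode lasts exactly d days, the share open is d/T and the mean recorded length is d − d²/(2T).

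- d = 14: 14/90 = 16% open; mean 12.9 days, an understatement of 8%.
- d = 28: 28/90 = 31% open; mean 23.6 days, an understatement of 16%.

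The share open barely changes, but the understatement of the mean is about half as large.

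**Effect on a comparison by ANOVA.** Take two impact categories with exponential means of 28 and 14 days, a true difference of 14 days. The recorded difference is 19.6 − 11.8 = 7.8 days.

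**Effect on a logit.** Take the outcome of pain lasting more than 28 days, with an exponential mean of 28 days. The true probability is exp(−1) = 37%. Only onsets in the first 62 of 90 days can show it, so the recorded probability is 0.368 × 62/90 = 25%. With a threshold of 7 days, only onsets in the last 7 of 90 days (8%) are affected.

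**Effect of onset day.** With a mean of 30 days, the expected recorded length is 30 × (1 − exp(−85/30)) = 28.2 days for onset on day 5, and 30 × (1 − exp(−10/30)) = 8.5 days for onset on day 80. An early episode is capped, not made short. The large loss needs a late onset or a length close to the remaining window.

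**The case against.** The strongest reply is that the article condenses the plan into one sentence on methods. It does not say how duration is derived. Duration may be a self-reported item or a set of categories, and a full analysis plan, not shown, may treat open episodes as censored. So a reader might infer that the plan enters open episodes as complete, but the article does not say so, and the point has to stay conditional. What stands is that the article does name the methods for duration, and those methods do not handle right-censoring as they come. That is a stated choice that fits the outcome badly, not merely a detail left out.

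A second reply is that the study is described as one of acute effects, and pain that lasts days is hardly touched. This is right, and the low end of the table shows it.

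Two stronger readings are tempting and fail:

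- A reader might infer that two months in Target sample size contradicts day 90 in Table 1, and that some participants stop at day 60. The wording there sets a minimum, which 90 days satisfies. Basing power on it is conservative, and nothing schedules a stop at day 60.
- A reader might infer that particular impact types will look harmless because they occur late. Day 90 is counted for each participant, and enrolment is staggered from August 2024 towards June 2027. The article gives no reason why any impact type should cluster late in individual windows. Truncation unrelated to impact type weakens contrasts in general and does not single out particular impacts.

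**Conclusion.** The point holds in conditional form. Duration is an analysed outcome, logging ends at study day 90 regardless of episode status, and the named models take no account of episodes still open. If logged lengths are used as they stand, mean durations are understated by about 3% to 8% when episodes average 3 to 7 days, and by about 16% to 32% when they average 14 to 30 days. Differences between exposures shrink accordingly.

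These sizes rest on uniform onset and exponential durations, and on episode lengths that the documents do not supply. With fixed lengths the understatement is about half. Whether the bias matters in practice depends on how much of the reported pain persists for weeks. Since the correction is cheap, it is worth making before the data are analysed.

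**What to change.** In Statistical methods, replace ANOVA or logit on recorded length, for this outcome only, with an analysis of time from onset to return to the participant's own baseline pain level. Table 1 already schedules a VAS reading at allocation that can serve as the baseline. Treat episodes open at the last log, at day 90 or at earlier drop-out, as right-censored. Kaplan-Meier curves and Cox models with clustering by participant would do, since one operator may contribute several episodes. Report the number of episodes open at the last log. ANOVA and logit models can stay for intensity and location.

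The cost is one different model for one outcome, with no new data and no change to the 192. Censoring at day 90 is administrative and should do little harm. Censoring at drop-out is less secure, because the article itself expects poorer logging from participants without pain, and this should be acknowledged when results are reported.

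Continuing the log beyond day 90 for participants with open pain would capture more complete episodes, but it is a separate decision. It would change follow-up in a study that is already enrolling. If exposure were no longer measured, continuing pain could not be told apart from the effect of new impacts. The analysis change does not depend on it.

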## Discussion

This study provides a comprehensive approach to evaluating human impact exposure onboard high-speed boats. By incorporating objective measurement tools such as triaxial accelerometers and self-reported pain assessments, it aims to identify risk factors and inform future safety measures. However, several limitations must be considered when interpreting the findings.

One key limitation is the observational nature of the study, which prevents definitive conclusions about causality between impact exposure and musculoskeletal injuries. While correlation analyses will be conducted, future interventional studies are necessary to confirm causal relationships. Additionally, the study relies on self-reported pain assessments, which are subject to recall bias and individual pain perception variations, potentially leading to inconsistencies in data reporting.^29^

The study population is restricted to professional high-speed boat operators, limiting the generalisability of findings to other groups such as recreational users or operators in different occupational settings. Furthermore, differences in operational environments, including boat types, sea conditions and mission profiles, may introduce variability in exposure levels, making it challenging to standardise impact measurement across all study sites.

Confounding variables such as pre-existing musculoskeletal conditions, overall physical fitness and variations in operator experience could influence the outcomes despite efforts to control for these factors.^30^ Additionally, compliance with daily pain logging through the smartphone application may fluctuate, leading to potential gaps in data collection that could affect the robustness of findings.

Another limitation is the potential impact of national and organisational differences in health and safety regulations. Since multiple countries and agencies are involved, variations in operational protocols and exposure limits may affect how findings are interpreted and applied to different regulatory frameworks.

At last, while the use of accelerometers provides precise impact exposure data, the interpretation of biomechanical forces and their effects on human physiology remains complex. Future research should aim to refine exposure thresholds and explore biomechanical modelling to better predict injury risks.

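### The plan promises to establish safe impact levels from which characteristics correlate with pain, but correlation findings from a study sized to detect a difference cannot show safety

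*Protocol article*

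**What the plan says.** The Statistical methods section lists four analytical steps:

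- Screening: "A data analysis engine will categorise impacts with various combinations of the impact characteristics", so that these can be correlated with the pain records.
- Simple association: "We will use Pearson correlation coefficients to examine the association between human impact exposure and pain scores".
- Adjustment: "We will also use linear regression to examine these associations while controlling for potential confounding variables".
- Multivariable work: ANOVA is planned; in addition, "logit models will be used to identify which characteristics of the impacts correlate to reported pain of various intensities, locations and durations after exposure".

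Taken together, these steps are "expected to indicate which impact characteristics show a correlation to reported experiences of pain". The next sentence draws the conclusion: "Based on these findings, we will establish which impact exposure levels and characteristics are safe regarding physical and cognitive capabilities".

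The article names no acceptable risk, no pain increase to be excluded, and no rule that turns an association into a level. The Target sample size section rests on a 14 mm VAS difference. The Discussion is more cautious: it says the observational design "prevents definitive conclusions about causality between impact exposure and musculoskeletal injuries", and it leaves the refinement of thresholds to later research.

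**The concern.** The planned findings are a list of characteristics that correlate with pain. Safety is a different kind of claim: it needs evidence that the excess harm at a given exposure is smaller than some tolerable amount. Three gaps separate the two.

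1. A correlation that is not detected may be a correlation the study could not see.
2. A Pearson coefficient or a single linear slope summarises the whole exposure range in one number. On its own it does not say where harm begins.
3. The safety statement covers cognitive as well as physical capability, but the findings it rests on concern pain. Table 1 lists only a questionnaire, the VAS and the pain drawing.

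The Discussion foresees that the results could inform training limits, standards for safe operation, and dashboard instruments that tell crews when impacts become dangerous. If a harmful exposure were called safe on the strength of a weak or absent correlation, the error could reach the people exposed.

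**Working it through.** **Step 1. What the study is sized for.** Inputs from Target sample size: difference 14 mm, SD 20 mm, alpha 0.05 (taken as two-sided), power 80%, 1.1 injuries per person-year, follow-up of 2 months, one operator in six injured.

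- Expected injuries in 2 months: 1.1 × 2/12 = 0.183. Probability of at least one: 1 − exp(−0.183) = 0.168, about 1/6.
- Per group: n = 2 × [20 × (1.960 + 0.842)/14]² = 32.04.
- Inflated for one in six: 32.04 × 6 = 192.2, against 192 stated.

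The figure reproduces. It is a calculation to detect a difference; nothing in it sets a bound on harm to be excluded.

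**Step 2. What an undetected correlation could hide (illustration).** Assumption: one summary value per participant, N = 192. Power = Φ(atanh(r) × √(N − 3) − 1.96), with √189 = 13.75.

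| True r | atanh(r) × 13.75 | Power | Missed |
|---|---|---|---|
| 0.10 | 1.38 | 28% | 72% |
| 0.15 | 2.08 | 55% | 45% |
| 0.20 | 2.79 | 80% | 20% |

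The smallest correlation with 80% power is tanh(2.802/13.75) = 0.20.

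The same point on injury risk, assuming 96 lower-exposed and 96 higher-exposed operators with a mean 2-month risk of 1/6: a doubling of risk (11.1% against 22.2%) has 54% power, so it is missed 46% of the time. No injuries among 32 operators in an exposure band would still allow a risk of up to 1 − 0.05^(1/32) = 8.9% (one-sided 95% limit).

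**Step 3. What a coefficient says about a level (illustration).** Assumptions: peak acceleration of 2g plus a gamma variable (shape 4, scale 1), clipped at 25g; pain SD 20 mm; r fixed at 0.20. The effect that produces this r is 0.20 × 20/(c × s), where c is the correlation of the response shape with exposure and s is the SD of that shape.

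| Response shape | c | Effect giving r = 0.20 |
|---|---|---|
| Linear | 1.00 | 2.0 mm per g |
| Step at 5g | 0.70 | 11.9 mm |
| Step at 8g | 0.75 | 15.0 mm |
| Step at 10g | 0.57 | 35.0 mm |

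Four different answers to the question of where pain begins share one coefficient.

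**Step 4. The sentence against the rest of the article.** The Introduction aims to find impacts that are potentially harmful. The Discussion says the data can indicate such levels and be used to suggest training limits, calls interventional studies necessary to confirm causation, and defers the refinement of thresholds. Only the Statistical methods sentence says that safe levels will be established.

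**The case against.** **No written rule equates non-significance with safety.** A reader might infer that every characteristic failing a significance test will be labelled safe. The article does not say so and gives no significance rule for classifying characteristics. This stands. What remains is that safety is to be established from findings about correlation, with no other basis named.

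**The plan has more than Pearson coefficients.** Categorised impacts, ANOVA and logit models could give risk by level, and a full plan may say how. This stands too, so it would be wrong to say the study cannot produce levels. But the section puts these models to identifying which characteristics correlate, and the concluding sentence rests on that.

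**The miss rates assume a design the article does not describe.** The study is self-controlled with daily logging. At 24 logged days a month, 192 participants give 24 × 2 × 192 = 9,216 entries over 2 months. If these were worth 500 to 1,000 independent observations (an assumption), r = 0.10 would be missed about 39% to 11% of the time. At 500, r = 0.15 would be missed about 8% of the time. The objection is fair, and the rates in the working are illustrative only. Greater power narrows the interval, but it still takes the interval, set against a stated bound, to support a claim of no important harm.

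**Multiplicity.** A reader might multiply characteristics by channels by pain variables to count false positives. The article's definitions do not support such a count: the number and duration of impacts are defined on the vertical hull signal only, and the vector sum merges three axes into one value. Nor does it say outright that metrics picked by screening will be validated on the same data; the validation it mentions concerns alternative units of exposure.

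**The study calls itself exploratory.** It does, and that is a reason not to promise that safe levels will be established.

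**Conclusion.** The concern holds in this form. The concluding sentence of the planned analysis promises a safety classification that its stated basis cannot deliver. An undetected or weak correlation does not show safety, a coefficient or slope alone fixes no level, and the sample size is built to detect 14 mm rather than to exclude harm. The sentence also exceeds the article's own Introduction and Discussion. Followed as written, it could give an unsound conclusion.

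How often a real association would be missed cannot be fixed from the article, because the unit of analysis and the within-person correlation are not given. The conclusion does not depend on any one of those rates.

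**What to change.** Replace the safety sentence in Statistical methods as follows.

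1. State that the study will estimate exposure-response, that is, pain by exposure level compared with the same person's unexposed days, with confidence limits, and will identify exposures associated with pain.
2. Describe a level as having no important excess pain only where the upper confidence limit of the excess proportion of person-days (or operators) with a clinically important VAS rise, using the plan's own 14 mm, lies below a bound stated in advance. The investigators must choose that bound.
3. Report every other level as not established, and drop the promise to establish what is safe, including for cognitive capability.
4. Present metrics picked by screening many combinations as exploratory, not validated. Confirming them in left-out centres is optional.

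The criterion should be a proportion and not the mean VAS rise. If one operator in six rises by 60 mm and the others do not change, the mean rise is 60/6 = 10 mm, which is below 14 mm. A rule on the mean could clear a level at which a minority is badly affected.

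Cost: analysis and wording only, with no new data. Fewer levels can be cleared, and the bound has to be agreed before the data are examined.

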## Abstract

**Introduction:**

High-speed boat operations expose personnel to slamming-induced impacts, which can lead to musculoskeletal injuries and cognitive impairments. Despite existing safety measures, regulations and protocols, the risk of injuries remains significant. The MultiAgency, prospective, exploratory, non-intervention, cohort Study on Human Impact Exposure oNboard high-speed boats study aims to investigate the nature and magnitude of these impacts, their acute and long-term health effects, and potential injury prevention strategies to improve operational safety and performance.

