#### Health and working conditions survey

A validated web-based questionnaire for surveying the health and working conditions of high-performance marine craft populations will be designed to assess a range of factors, including musculoskeletal injuries, noise exposure, psychological stress and fatigue.^12^

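### The plan would declare exposure levels safe for cognition from correlations with pain, and the article names no cognitive measure or cognitive analysis

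*Protocol article*

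**What the plan says.** All references are to the protocol article.

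- **Objective.** Study design, setting and participants says that the study "investigates the acute effects of slamming-induced impact exposure on high-speed boat operators’ musculoskeletal systems and cognitive functions".
- **Conclusion.** Statistical methods ends its main paragraph with the statement that "we will establish which impact exposure levels and characteristics are safe regarding physical and cognitive capabilities". The statement is explicitly based on the findings in the sentence before it: "The results of the statistical analysis are expected to indicate which impact characteristics show a correlation to reported experiences of pain".
- **Assessments.** Table 1 schedules a questionnaire (allocation and close-out), pain intensity on a VAS and a pain drawing (both at allocation and then daily). Its footnote says that the timepoints "define days 1–90".
- **Questionnaire content.** Health and working conditions survey describes a range of factors, "including musculoskeletal injuries, noise exposure, psychological stress and fatigue".
- **Abstract.** Its introduction says that the study "aims to investigate the nature and magnitude of these impacts, their acute and long-term health effects".

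**The concern.** A conclusion about safety needs data on the outcome that is called safe. Here cognition is both an object of study and part of the final conclusion, but the only evidence cited for that conclusion is pain. An operator can be free of pain and still be cognitively impaired. The article's own Introduction reports impaired cognition and even loss of consciousness after exposure, and nothing in the document argues that pain can stand in for these.

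The Discussion says that the results can be used to suggest limits for training, to guide standards, and to calibrate dashboard warnings. A threshold described as safe for cognition on pain data alone could give false reassurance in any of these uses.

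**Working it through.** The point turns on whether the stated conclusion has a stated outcome behind it. The article's one design figure is checked first, to see which endpoint it serves.

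**Sample size.** Inputs from Target sample size: difference 14 mm, SD 20 mm, power 80%, significance level 0.05 (taken as two-sided, since the article does not say), and one operator in six with an episode.

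- Share with an episode: 1.1 injuries per person-year × 2/12 = 0.183 expected injuries; 1 − exp(−0.183) = 0.168, about one in six.
- Per group, two means, normal approximation: 2 × [20 × (1.960 + 0.842) / 14]² = 32.04.
- Total: 32.04 × 6 = 192.2, which matches the stated 192.

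The figure reproduces, and every input is an injury rate or a back-pain quantity. No cognitive endpoint enters it.

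**Where a cognitive outcome could appear:**

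| Place in the article | What it names | Cognitive measure named? |
|---|---|---|
| Table 1 | Questionnaire, pain VAS, pain drawing | No |
| Pain | Location, modality, intensity and duration of pain | No |
| Health and working conditions survey | Injuries, noise, stress, fatigue (open list) | No |
| Risk of bias, confounding factors and compliance | Free text on onboard events and outside activities; questionnaire for baseline health | No |
| Statistical methods | Pearson correlation, linear regression, ANOVA and logit models, all relating exposure to pain | No |
| Subgroup analysis | Differences in the association of exposure with pain scores | No |

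**The inference.** The conclusion sentence rests on the findings of the sentence before it. Those findings concern pain. The premise therefore holds no cognitive information, whereas the conclusion does. A more detailed analysis of the same pain data would not close that gap.

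**Long-term effects.** The abstract mentions "their acute and long-term health effects". The design statement in the body says acute effects, the two numbered aims at the end of the Introduction do not mention long-term effects, and Table 1 closes at day 90. Target sample size speaks of at least 2 months of follow-up, which is a minimum, but no assessment after day 90 is described. This is a mismatch between abstract and body.

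**The case against.** The strongest objection is that the questionnaire's list of factors is open. The instrument is cited rather than shown, and a condensed article need not print its items. An unnamed cognitive item therefore cannot be excluded. This stands: a reader might infer that the study collects no cognitive data at all, and the article does not support that. It supports only that none is named.

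Such an item would not rescue the conclusion, however. The questionnaire is given at allocation and at day 90, which is poorly timed for acute effects of individual exposures. Its only stated role in the analysis is to establish baseline health because of confounding. The conclusion sentence itself draws on the pain findings and not on the questionnaire.

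A second objection is that the article is cautious elsewhere. It disclaims causality in its strengths and limitations and again in the Discussion, where it also leaves the refinement of exposure thresholds to future research. The uses in training and operations are described as possibilities, so a reader who infers that agencies have committed to adopting the levels goes too far. That also stands. But neither list of limitations mentions the lack of a named cognitive outcome, and the conclusion sentence says that safe levels will be established.

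Third, a reader might infer that the study promises long-term conclusions. It does not: the only basis is one clause on aims in the abstract, and the body narrows the scope to acute effects.

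**Conclusion.** The point holds for cognition. Following the article as written leads to a statement that certain exposure levels are safe for cognitive capabilities, with correlations with pain as the only stated support. In size: none of the three scheduled assessments is described as measuring cognition, and no stated analysis has a cognitive outcome. The pain analyses, the sample size and the data collection are unaffected.

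The verdict rests on the article's text alone. It would change in part if the full protocol names a cognitive measure with suitable timing and an analysis. Even then the conclusion sentence would need rewording, because it derives cognitive safety from pain.

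The long-term wording is a minor inconsistency in the abstract and adds no weight to the main point.

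**What to change.** 1. In Statistical methods, delete the words *and cognitive* from the conclusion sentence and add: *Conclusions are limited to self-reported pain within the 90-day schedule; absence of pain is not evidence of cognitive safety.*
2. In Study design, setting and participants, remove *cognitive functions* from the statement of what is investigated. Keep it only if a cognitive measure already being collected can be named, with its timing relative to exposure and the analysis that uses it.
3. Minor: in the abstract, bring the reference to long-term effects into line with the acute effects named in the body and the day-90 close-out.

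**Cost.** The edits need no new data and leave the 192 participants unchanged. The downside is a narrower claim and, if nothing can be named under item 2, the loss of a stated objective. Because enrolment began on 23 August 2024, that loss should be recorded as a change to the plan and not made silently. Inclusion is expected to stay open until mid-2027, so there is time to do this before results are reported.
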